# Therapeutic hypothermia after nonshockable cardiac arrest: the HYPERION multicenter, randomized, controlled, assessor-blinded, superiority trial

**DOI:** 10.1186/s13049-015-0103-5

**Published:** 2015-03-07

**Keywords:** Cardiac arrest, Therapeutic hypothermia, Nonshockable rhythm

## Abstract

**Background:**

Meta-analyses of nonrandomized studies have provided conflicting data on therapeutic hypothermia, or targeted temperature management (TTM), at 33°C in patients successfully resuscitated after nonshockable cardiac arrest. Nevertheless, the latest recommendations issued by the International Liaison Committee on Resuscitation and by the European Resuscitation Council recommend therapeutic hypothermia. New data are available on the adverse effects of therapeutic hypothermia, notably infectious complications. The risk/benefit ratio of therapeutic hypothermia after nonshockable cardiac arrest is unclear.

**Methods:**

HYPERION is a multicenter (22 French ICUs) trial with blinded outcome assessment in which 584 patients with successfully resuscitated nonshockable cardiac arrest are allocated at random to either TTM between 32.5 and 33.5°C (therapeutic hypothermia) or TTM between 36.5 and 37.5°C (therapeutic normothermia) for 24 hours. Both groups are managed with therapeutic normothermia for the next 24 hours. TTM is achieved using locally available equipment. The primary outcome is day-90 neurological status assessed by the Cerebral Performance Categories (CPC) Scale with dichotomization of the results (1 + 2 versus 3 + 4 + 5). The primary outcome is assessed by a blinded psychologist during a semi-structured telephone interview of the patient or next of kin. Secondary outcomes are day-90 mortality, hospital mortality, severe adverse events, infections, and neurocognitive performance. The planned sample size of 584 patients will enable us to detect a 9% absolute difference in day-90 neurological status with 80% power, assuming a 14% event rate in the control group and a two-sided Type 1 error rate of 4.9%. Two interim analyses will be performed, after inclusion of 200 and 400 patients, respectively.

**Discussion:**

The HYPERION trial is a multicenter, randomized, controlled, assessor-blinded, superiority trial that may provide an answer to an issue of everyday relevance, namely, whether TTM is beneficial in comatose patients resuscitated after nonshockable cardiac arrest. Furthermore, it will provide new data on the tolerance and adverse events (especially infectious complications) of TTM at 32.5-33.5°C.

**Trial registration:**

ClinicalTrials.gov: NCT01994772.

This manuscript was written in accordance with SPIRIT guidelines [1].

## Introduction

### Background and rationale

Cardiac arrest remains a major cause of mortality, as well as a cause of disability in survivors [2]. In Europe, 300 000 cardiac arrests occur annually, of which 250 000 are fatal. Even among patients with good prognostic factors, less than 50% are discharged from the hospital without severe neurological impairments [3,4].

After early work suggesting a neuroprotective effect of hypothermia [5], animal studies provided evidence of neurological recovery after a period of controlled hypothermia [6]. These findings were confirmed by two randomized trials performed 10 years ago and published in the same issue of the *New England Journal of Medicine*. In both trials, therapeutic hypothermia significantly improved the neurological outcomes of patients with cardiac arrest in shockable rhythms (ventricular fibrillation or pulseless ventricular tachycardia). The first randomized trial was a European multicenter study in 275 patients managed with normothermia or hypothermia [7]. After 6 months, the proportion of patients with good neurological outcomes was 55% with hypothermia compared to only 39% with normothermia (odds ratio [OR], 1.4; *P* = 0.009). In addition, mortality was significantly lower in the hypothermia group (OR, 0.74; *P* = 0.02). The second randomized trial was an Australian multicenter study in 77 patients managed with normothermia or hypothermia [8]. Again, good neurological outcomes were more common in the hypothermia group (OR, 1.88; *P* = 0.046), and this difference persisted in the multivariate analysis (OR, 5.25; *P* = 0.011). However, hypothermia was not associated with a significant decrease in mortality (OR, 1.75; *P* = 0.145). A 2012 Cochrane review and metaanalysis confirmed the neuroprotective effect of hypothermia (relative risk [RR] of achieving a good neurological outcome, 1.55; 95% confidence interval [95% CI], 1.22-1.96) [9].

These data firmly establish the efficacy of TTM between 32°C and 34°C in improving the neurological outcomes of patients with shockable cardiac arrest. Guidelines issued in 2010 by the European Resuscitation Council (ERC) [10] and International Liaison Committee on Resuscitation (ILCOR) [11] recommend the routine use of TTM between 32°C and 34°C in comatose survivors of cardiac arrest with a nonshockable rhythm at arrival of emergency-care providers. These recommendations are based on a low level of evidence (Class IIb, LOE B). No randomized trials have assessed therapeutic hypothermia in survivors of nonshockable cardiac arrest. The recommendations are based on retrospective cohort studies and on prospective studies evaluating the feasibility of achieving a period of 32°-34° TTM using invasive [12] or semi-invasive [13] devices. Nevertheless, the results of these studies are conflicting.A metaanalysis [14] showed no significant improvement in the 6-month neurological outcomes of 897 patients included in retrospective cohorts (OR, 0.93; 95% CI, 0.88-1). In addition, two recent prospective cohort studies not included in the meta-analysis -- one from France published in *Circulation* [15] and the other from Finland published in *Intensive Care Medicine* [16] -- failed to demonstrate benefits from 32°-34° TTM in survivors of nonshockable cardiac arrest. Two German studies [17,18], one retrospective and the other prospective, showed no decrease in mortality when 32°-34° TTM was combined with optimal post-cardiac arrest care (including prompt coronary angiography if appropriate and hemodynamic parameter optimization). A very recent post-hoc analysis of the randomized TTM Study [19] showed no difference in neurological outcomes in the 178 patients with nonshockable rhythms [20].Other studies exhibiting similar methodological weaknesses (retrospective or prospective nonrandomized design without blinded assessment), in contrast, suggest a beneficial effect of hypothermia. Two retrospective Austrian studies showed better neurological outcomes with 32°-34° TTM in 374 patients [21] and 828 patients [22], respectively, with shockable or nonshockable cardiac arrest. Finally, a case–control study of 100 patients with nonshockable cardiac arrest reported by an American group showed better neurological outcomes with 32°-34° TTM [23].

Three factors probably explain most of the difference in 32°-34° TTM effects between patients with shockable versus nonshockable cardiac arrest. First, patients with shockable cardiac arrest constitute a fairly uniform population of predominantly male individuals with a cardiac cause (ST-segment-elevation myocardial infarction) potentially treatable by coronary angiography and appropriate percutaneous coronary intervention [24]. In contrast, nonshockable cardiac arrest can occur in a wide variety of settings, for instance as a complication of a primary shockable rhythm or during asphyxia due to hanging, drowning, or gastric-content aspiration. Second, nonshockable cardiac arrest carries a poorer prognosis than does shockable cardiac arrest: survival with good neurological function (CPC 1 or 2) is nearly 40% after shockable cardiac arrest compared to less than 20% after nonshockable cardiac arrest [25,26]. Two factors associated with a better prognosis of cardiac arrest are less common in nonshockable than shockable rhythms, namely, presence of a witness [27] and cardiac origin of the arrest [28]. Consequently, demonstrating a beneficial effect of a therapeutic intervention requires a larger sample size in studies of nonshockable compared to shockable cardiac arrest. Third, a corollary to the first and second factors is that the effects of interventions for cardiac arrest may differ markedly between patients with nonshockable and shockable cardiac arrest. For example, although recent data argue against epinephrine treatment during shockable cardiac arrest [29,30], other studies strongly support the earliest possible administration of epinephrine during nonshockable cardiac arrest [31].

Studies of neonatal hypoxia have produced convincing evidence that 32°-34° TTM diminishes mortality and improves neurological outcomes [32,33]. Although brain plasticity differs between neonates and adults, this evidence strongly supports a beneficial effect of 32°-34° TTM in patients with cardiac arrest due only to anoxia. A retrospective study showed that the mortality rate after attempted suicide by hanging with cardiac arrest was as high as 90% [34]. In contrast, in two studies of 32°-34° TTM used to treat patients with severe asphyxia, mortality was less than 67% [35] and 45% [36], respectively. These findings support evaluation of 32°-34° TTM in patients with nonshockable cardiac arrest due to noncardiac causes [37].

The safety profile of 32°-34° TTM was good in two early studies [7,8]. More recently, however, an increased risk of infection [38], including pneumonia [39] was reported. In addition, 32°-34° TTM usually requires neuromuscular blockade, which interferes with the neurological assessments, thereby extending ICU stay length and diminishing the ability to identify seizures and to provide optimal seizure prevention [40]. Activation of the inflammatory cascade may occur during 32°-34° TTM [41], leading to a risk of rebound hyperthermia, which may adversely affect patient outcomes [42,43]. Similarly, 32°-34° TTM may exert negative hemodynamic effects, increasing vasoactive drug requirements [44], a point of particular concern given the poor prognosis of post-resuscitation shock [16].

In sum, the risk/benefit ratio of 32°-34° TTM in patients with nonshockable cardiac arrest remains unclear. This uncertainty has led to a call for randomized controlled trials [45].

### Objectives

#### Primary objective

To determine whether TTM between 32.5°C and 33.5°C (32.5°-33.5° TTM) for 24 h improves day-90 neurological outcomes compared to TTM between 36.5°C and 37.5°C in survivors of nonshockable cardiac arrest.

#### Secondary objectives

To determine whether 32.5°-33.5° TTM for 24 h decreases mortality and morbidity (ICU and hospital stay lengths) and to assess the safety of 32.5°-33.5° TTM.

### Trial design

HYPERION is a multicenter, randomized, controlled, assessor-blinded, superiority trial with two parallel groups and a primary endpoint of day-90 neurological outcome.

## Methods: participants, interventions, and outcomes

### Study setting

The HYPERION trial is taking place in 22 ICUs in 22 hospitals (8 university and 14 general hospitals) in France.

### Eligibility criteria

Figure 1 shows the patient eligibility criteria and study protocol.

**Figure 1 Fig1:**
[figure not shown]
**Study flowchart.** ICU, intensive care unit; RRT, renal replacement therapy.

#### Inclusion criteria

Patients must meet both of the following criteria:Cardiac arrest in nonshockable rhythm andGlasgow Coma Scale score ≤8. In patients receiving sedative therapy at ICU admission, the Glasgow Coma Scale score assessed by the emergency physician just before sedative therapy initiation is used.

#### Exclusion criteria

Patients fulfilling one or more of the following criteria are not included:No-flow time >10 min (time from collapse to initiation of external cardiac massage);Low-flow time >60 min (time from initiation of external cardiac massage to return of spontaneous circulation).Major hemodynamic instability (defined as a continuous epinephrine or norepinephrine infusion at a flow rate >1 μg/Kg/min)Time from cardiac arrest to study inclusion >300 minMoribund patientChild C cirrhosis of the liverAge <18 yearsPregnant or breastfeeding womanCorrectional facility inmatePrevious inclusion in another randomized clinical trial on cardiac arrest with day-90 neurological outcome as the primary endpointPatient without health insuranceDecision by the patient or next of kin to refuse the study.

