#### Concomitant prevention of systemic secondary brain injury in both groups

##### Arterial hypotension

Hemodynamic evaluations are conducted to allow blood volume optimization. Hypovolemia is managed with crystalloid or colloid infusion, according to standard practice in the participating ICU. Subsequent evaluations are performed as dictated by the course of the hemodynamic parameters. In accordance with guidelines [10], and in the absence of specific randomized studies, a mean arterial pressure of 65 mmHg and, if measured, central venous oxygen saturation (ScvO_2_) ≥70% are considered reasonable targets [11]. The introduction of vasoactive drug treatment is at the discretion of the physicians, who follow international guidelines [10] and local protocols.

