### Sample size

We expect that 14% of patients in the 36.5°-37.5° TTM group will be CPC 1 or 2 on day 90 and that this proportion will increase by 9% with 32.5°-33.5° TTM. With a two-sided Type I error of 5% and 80% power, and given that two interim analyses will be performed, the required number of patients is 292 per group, i.e., 584 patients in all.

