### Statistical methods

#### Statistical analysis

A predefined statistical analysis plan will be followed. The intention-to-treat principle will be applied. The statistical report will incorporate the data recommended by the CONSORT Statement extension for nonpharmacologic treatment interventions [72].

Descriptive statistics will be used to compare the two randomization groups, without statistical testing. The chi-squared test will be performed to compare the primary endpoint in the two groups. Two interim analyses will be conducted, after the inclusion of 200 and 400 patients, respectively. The rule developed by Peto and Haybittle [73] will be applied, with the significance level set at 0.001 for both interim analyses and the significance level associated with the final analysis set at 0.049 to maintain an overall Type I error of 5%.

Secondary endpoints evaluating binary variables (need for renal replacement therapy, acute cardiogenic pulmonary edema, and binary day-90 neurological outcome) will be compared using the chi-squared test. Secondary endpoints evaluating quantitative variables (biological tests, stay lengths, and mechanical ventilation duration) will be compared using the Student t test or Mann–Whitney test.

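### Patients already on a vasoactive infusion at randomization count as events in both arms of the 48-hour vasoactive-need outcome, which dilutes the hemodynamic safety comparison toward no difference

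*Protocol article*

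**What the plan says.** Three parts of the protocol article bear on this point.

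- **Exclusion criteria.** A patient is excluded for "Major hemodynamic instability (defined as a continuous epinephrine or norepinephrine infusion at a flow rate" greater than 1 μg/kg/min. A lower rate does not exclude. Inclusion may take place up to 300 minutes after the arrest, so an infusion can already be running.
- **Secondary outcome measures.** The list includes the need for vasoactive drugs during the first 48 hours. The entry is not limited to new or increased need, carries no dose or duration, and does not set aside patients already treated. It does not say when the 48 hours begin.
- **Background and rationale.** Cooling to 32°-34° "may exert negative hemodynamic effects, increasing vasoactive drug requirements", which the article calls "increasing vasoactive drug requirements [44], a point of particular concern given the poor prognosis of post-resuscitation shock".

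Under Arterial hypotension, "The introduction of vasoactive drug treatment is at the discretion of the physicians". The Statistical analysis section assigns the chi-squared test to binary secondary endpoints. The Allocation, Statistical analysis and Subgroup analysis sections do not mention stratification, adjustment or subgrouping by vasoactive treatment at randomization.

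**The concern.** The harm described in the Background is one of degree: cooled patients may require more vasoactive support. The outcome asks only whether support was needed at all. A patient on norepinephrine at randomization answers yes whichever temperature is assigned, and a later dose increase does not alter the answer. The unstated start of the 48 hours makes no difference. Whether counted from the arrest, ICU admission or randomization, the window includes an infusion that is running at randomization.

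What is at stake is how a null result would be read. The trial's rationale is an unclear risk/benefit ratio, and safety is among its secondary objectives. A real increase in vasoactive requirement could be reported as no difference between arms partly because many patients could not differ on this measure.

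**Working it through.** **The plan's own figure.** The Sample size section gives 14% in the control group, a 9-point increase (so 23%), two-sided 5% and 80% power. With the pooled-variance formula and mean proportion 0.185:

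n = [1.960 × √(2 × 0.185 × 0.815) + 0.8416 × √(0.14 × 0.86 + 0.23 × 0.77)]² / 0.09² = (1.0763 + 0.4590)² / 0.0081 = 291.02, rounded up to 292.

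This reproduces "the required number of patients is 292 per group, i.e., 584 patients in all". (At 0.049 it gives 293.) The figure concerns the primary endpoint; it is used here only as the number per arm.

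**Dilution.** Let b be the share on an infusion at randomization, the same in expectation in both arms. Let q0 and q1 be the proportions of the remaining patients who start a vasoactive drug within 48 hours under normothermia and hypothermia.

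- Control rate as written: b + (1 − b)q0
- Hypothermia rate as written: b + (1 − b)q1
- Difference: (1 − b)(q1 − q0)

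**Inputs that are assumptions.** The documents give neither b nor q. Take q0 = 30% and q1 = 42%, and vary b from 0.3 to 0.7.

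**Power.** Power = Φ[(d − 1.96 × SE0)/SE1], with SE0 the pooled and SE1 the unpooled standard error, two-sided alpha 0.05.

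Worked case, b = 0.5:

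- As written, 292 per arm: 65% v 71%, d = 0.06, SE0 = √(2 × 0.68 × 0.32/292) = 0.0386, SE1 = 0.0385. (0.06 − 0.0757)/0.0385 = −0.41, so power is 34%.
- New starts only, 146 per arm: 30% v 42%, d = 0.12, SE0 = √(2 × 0.36 × 0.64/146) = 0.0562, SE1 = 0.0557. (0.12 − 0.1101)/0.0557 = 0.18, so power is 57%.

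| b | As written, 292 per arm | Difference | Power as written | Untreated at entry, per arm | Power, new starts |
|---|---|---|---|---|---|
| 0.3 | 51.0% v 59.4% | 8.4 points | 53% | 204 | 72% |
| 0.5 | 65.0% v 71.0% | 6.0 points | 34% | 146 | 57% |
| 0.7 | 79.0% v 82.6% | 3.6 points | 20% | 88 | 38% |

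**Other assumed effects, at b = 0.5.** With 30% v 45%, power is 50% as written and 76% for new starts. With 40% v 50%, it is 27% and 40%.

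**Why the subset does better with fewer patients.** Write q̄ for the mean new-start rate and p̄ = b + (1 − b)q̄ for the mean rate as written. Because 1 − p̄ = (1 − b)(1 − q̄), the pooled test statistic as written equals √(q̄/p̄) times the statistic in the subset. At b = 0.5 this is √(0.36/0.68) = 0.73. Since p̄ exceeds q̄ whenever b is above zero, the direction does not depend on the assumed rates; only the size does.

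**The case against.** The outcome is a single line in a condensed article. The full protocol, the eCRF or the analysis plan may define it as new or increased need, which would remove the problem. The yes/no reading is an inference: the examples of binary endpoints in the Statistical analysis section do not include vasoactive need. This is one of about twenty secondary outcomes and is not among the safety results named for the monitoring board. Pulmonary edema, arrhythmia, renal replacement and mortality also bear on circulatory safety. Every rate above is assumed, and even the new-start analysis reaches only 38% to 72% power.

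Much of this stands, and it limits the weight of the point. It does not remove it. Yes/no is the natural reading of need, and the wording that is given, not a missing detail, fails to match the increase feared in the Background.

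Three stronger readings are tempting, and the documents support none of them.

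- A reader might infer that the outcome cannot detect hemodynamic harm at all. That is true only within the group already on an infusion. Patients untreated at randomization still contribute, so across the trial the effect is dilution.
- A reader might infer that patients already on an infusion are the ones most exposed to the harm. Nothing in the article shows this.
- A reader might infer that the exclusion threshold is at fault. It is not shown to be wrong; the mismatch lies in the outcome definition.

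**Conclusion.** The point holds as one of dilution in a secondary safety outcome. On the natural yes/no reading, patients on an infusion at randomization add equally to both arms, and the difference shrinks by exactly (1 − b). How much is lost depends on b and on the new-start rates, which the documents do not give. Under 30% v 42%, the outcome as written loses roughly 18 to 23 percentage points of power against the new-start analysis for b between 0.3 and 0.7 (72 − 53 = 19, 57 − 34 = 23, 38 − 20 = 18). These figures cover new starts only; dose increases in patients already treated are not quantified. The randomized comparison stays valid, and the primary analysis and sample size are unaffected. The change is worth making, but nothing else in the trial depends on it.

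**What to change.** In Secondary outcome measures, define the outcome, or add one beside the existing entry, as a new start of a vasoactive drug after randomization and within 48 hours, among patients not receiving one at randomization. State that the 48 hours run from randomization.

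Where infusion rates are recorded, also report in all patients the highest rate within 48 hours, adjusted for the rate at randomization, with a prespecified way of handling early death. This second measure is the one that captures escalation in patients already treated.

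Costs: the new-start analysis uses only part of the sample, but that part is fixed at baseline, so the comparison stays randomized. Vasoactive status at randomization must be in the eCRF or be retrieved from medical records, including for the 161 patients the article reports as already included by February 2, 2015. The peak-rate measure costs more: checking eligibility requires only knowing whether the threshold is exceeded, and Table 1 marks treatments from D0 without saying that rates are captured. Neither measure removes the influence of unblinded treatment decisions. No change to eligibility or to clinical management is implied.

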### Interventions

Patients allocated at random to 32.5°-33.5° TTM have hypothermia induced then maintained for 24 h. Slow rewarming to 36.5°-37.5° is then achieved and maintained for 24 h. Patients in the control group have their body temperature maintained at 36.5°-37.5°C for 48 h. Figure 2 provides details on the study protocol and randomization arms.

**Figure 2 Fig2:**
[figure not shown]
**Inclusion criteria related to the cardiac arrest and study procedures.** CA, cardiac arrest; CCCM, closed chest cardiac massage; ROSC, return of spontaneous circulation.

To induce and maintain 32.5°-33.5° TTM, each center follows its standard protocol. Thus, the method may involve active internal cooling using a specific device, active external cooling using a specific device, or active external cooling without a specific device. No trial using mortality or neurological outcome as the endpoint has demonstrated that one method is better than the others [46,47]. Infusion of cold fluid (4°C) is recommended to expedite achievement of the target temperature [48-50]. The same methods are used to manage hyperthermia (above 37.5°C) in both groups. The study protocol involves standardization of several parameters including sedation, neuromuscular blockade, and management of expected adverse events. The use of medications (e.g., acetaminophen or aspirin) to maintain normothermia is discouraged in both groups [51]. Figure 2 recapitulates the therapeutic interventions.

